### Control group

The control group will receive Treatment As Usual (TAU). The most common treatment for patients with MDD is a combination of medication, occupational therapy and a form of psychological treatment such as Cognitive Behavioral Therapy (CBT) or Problem Solving Treatment (PST). Nursing care focuses on assisting patients in their self-care activities, and encouraging them to participate in the unit’s daily activity program. Nurses also discuss the patient’s overall progress on a regular basis (weekly or biweekly). TAU is recorded at unit level. Before participating in the study, the units describe their treatment program for MDD using a structured form developed by the authors. This form is based on the NICE standard for MDD [7] and the Dutch guideline for MDD [29].

### Assessment

All patients will be assessed at baseline, after eight weeks, and after six months. Each assessment will involve patients filling in a questionnaire. At baseline, we will collect demographic data (gender, social status, education, and ethnicity) and some information about the disease history (former episodes of MDD, frequency and nature of former treatments [outpatient treatments and/or clinical admittance], and psychiatric co-morbidity).

### Primary outcome

Our primary outcome is the level of depression. This is measured by means of the Beck Depression Inventory, second edition (BDI-II-NL) [30,31]. The BDI-II is a self-report scale which contains 21 items clustered in four response categories. The BDI-II is divided into two components, an affective component (e.g. mood) and a physical component (e.g. loss of appetite). The cut off scores are: 0 – 13 for minimal depression, 14 – 19 for mild depression, 20 – 28 for moderate depression, and 29 – 63 for severe depression. The Dutch version of the BDI-II has a high internal consistency (Chronbach’s α ≥ 0.90) and a strong correlation with other depression instruments [32].

### Secondary outcome

Secondary outcomes are: level of activity, anxiety, mastery, quality of life, costs and health care use.

An Activity Log (AL) will be used to measure the level of activity. This is a form in which the patient fills in his or her activities over the past week. The AL contains a week schedule which is divided into morning, afternoon and evening activities. The patients will be asked to fill in the activities they have executed during the past week at baseline and after six months. The number of activities and the type of activity will be used to calculate the activity level of each patient.

The seven anxiety items of the HADS (Hospital Anxiety Depression Scale) [33] will be used to measure anxiety. A four-point Likert scale is used to score the items (0 – 3) and the total score therefore ranges from 0 (no anxiety) to 21 (very anxious). The cut-off score is ≥ 8, as an indication for an Anxiety Disorder.

Mastery will be measured by means of the Pearlin Mastery Scale [34]. This is a five-item self-report scale measuring internal locus of control. The items are presented as statements to be scored on a five-point Likert scale. The scores on the Pearlin Mastery Scale range from 5 (minimum level of mastery) to 25 (maximum level of mastery).

Quality of life will be measured by means of the SF 36 (MOS Short Forms Health Survey) [35]. The scale contains 36 questions divided into eight subscales with three underlying dimensions: (1) Functional Status: physical functioning (10 questions), social functioning (2 questions), role functioning – physical problems (4 questions), role functioning – emotional problems (3 questions); (2) Welfare: mental health (5 questions), vitality (4 questions), pain (2 questions); (3) Evaluation of health care: general health perception (5 questions), change in health care (1 question). The response options vary from dichotomous to a six-point Likert scale. The SF-36 was translated into Dutch by Van der Zee & Sanderman [36].

Costs will be measured by means of the TiC-P (Trimbos/iMTA questionnaire for costs associated with Psychiatric Illness) [37]. This questionnaire consists of two parts: direct costs of care consumption and indirect costs of care consumption. The TiC-P is a broad questionnaire which can be adjusted to the relevant population. This study will make use of the categories ‘care consumption’, ‘informal care consumption’, and ‘use of medication’. All items have dichotomous ‘yes/no’ response options. The questionnaire will be completed by the patient as a self-report instrument.

Table 1 provides an overview of the instruments.

**Table 1 T1:** Overview of instruments

**Time Instrument**	**Inclusion**	**T0**	**T1 = 8 weeks after T0**	**T2 = 6 months after T0**
Cognition: MMSE	X			
Diagnosis: MINI	X			
Baseline		X		
Depression: BDI-II-NL		X	X	X
Mastery: Pearlin Mastery Scale		X	X	X
Anxiety: HADS-A		X	X	X
Quality of life: SF-36		X	X	X
Health care costs: TiC-P		X		X
Activity Log		X		X

### Statistical analyses

The primary outcome is level of depression as measured with the BDI-II-NL. This outcome will be used to test the effect of the SAM as a nursing intervention in inpatient depressed elderly compared with TAU. The SAM is considered effective if there is a significant decrease in the level of depression in the treatment group compared to the control group. Because the patients will be randomized at unit level, multi-level analyses will be used to test the effects of the SAM intervention. In order to investigate differences in demographic and clinical variables, ANOVAs and Chi-square tests will be executed. Differences between the two groups in baseline characteristics will be corrected where necessary. For patient-oriented outcomes, Clinical Significant Change will be used [38,39].

Data will be analyzed according to the ‘intention-to-treat’ principle as well as the ‘completers only’ principle.

In order to correct for missing values, Last Observation Carried Forward and Multiple Imputation will be used as a sensitivity analysis.

Secondary outcome variables are quality of life (SF-36), costs (TiC-P), level of mastery (Pearlin Mastery Scale) and activities (Activity Log).

Anxiety is considered a co-variable because of its close association with MDD.

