### Sample size

Effect sizes (d) will be used to calculate the sample size. A meta-analysis by Cuijpers et al. [10] found an overall effect size of d = 0.87 in favor of Behavioral Activation (BA) compared to a waiting list condition. A study in an inpatient population found an effect size of d = 0.73 in favor of BA compared to supportive therapy [18].

Our study will be performed in an inpatient elderly population with severe MDD. Because of the large effect sizes in previous studies, an effect size of d = 0.7 is expected. With α = 0.05 and a power (1-β) of 0.8, 34 patients are needed per condition. In other studies [10,40], the dropout rate shows a large variability (2% – 50%). For this study, we assume an average drop-out rate of 25%. Another rule of the thumb is to increase the study population by 25% when patients are randomized at unit level. That means that 51 patients are required for each condition. In total, 102 patients will be included in this study. The sample size was calculated using the G*power 3.0 software program [41].

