## Discussion

This study will test Behavioral Activation (BA) as a nursing intervention in an inpatient elderly population. The study is innovative in two aspects. First, in previous studies psychologists with Master’s degrees carried out this intervention [10,11,18]. In our study, BA has been adapted to make it a nursing intervention – the SAM – to be carried out by registered nurses [28]. This makes BA more accessible for a larger group of patients.

Second, to our knowledge, most of the research on BA has mainly been conducted in outpatient adult populations. Only one other study [18] was executed in an inpatient adult population (N = 25) and, as far as we are aware, there are no studies in elderly inpatient populations. Studies in the elderly population are relatively scarce and have focused on outpatients [42,43] or depression in combination with dementia [44,45]. To our knowledge, this is the first BA effect study in an elderly inpatient population worldwide.

In addition to the innovative nature of this study, there are some difficulties concerning the study design. First, the study is vulnerable to selection bias. The SAM will be implemented in five mental health care units, and decisions regarding patient inclusion will depend partially on the anticipated efforts of the staff nurses. In order to minimize selection bias, the researcher will make an initial selection of eligible patients. Despite this, however, selection bias cannot be ruled out entirely, because it is ultimately the nurse who must motivate the patient to participate in the study, and this is expected to depend on the nurses’ belief that the SAM will be helpful for the patient. This may lead to selection bias in the experimental group, while the selection of patients in the control group will probably be free of bias. We will correct for any differences between the two groups in our statistical procedures.

This study will furthermore be vulnerable to information bias because a blind trial at intervention level is not possible. In order to avoid information bias, only self-report scales will be used in this study.

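### Observed baseline differences decide which covariates enter the primary analysis, and nothing commits to adjusting for baseline BDI-II

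*Protocol article*

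**What the plan says.** Three statements in the protocol article bear on covariate adjustment.

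- Statistical analyses, on comparing the arms: "In order to investigate differences in demographic and clinical variables, ANOVAs and Chi-square tests will be executed".
- The next sentence: "Differences between the two groups in baseline characteristics will be corrected where necessary".
- Discussion, after the authors explain that nurses may influence who joins in the experimental units: "We will correct for any differences between the two groups in our statistical procedures".

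No list of variables and no threshold is given. The two correction statements differ in scope: one applies only when needed, the other to every difference.

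Multi-level analysis is announced for the SAM effect only. The Statistical analyses section also names anxiety as a co-variable because of its association with depression. Table 1 schedules HADS-A and BDI-II at T0, T1 and T2. The article does not say which anxiety value is the covariate, or how the T0 BDI-II score enters the primary model.

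**The concern.** Whether a baseline variable differs between arms says little about whether it predicts the outcome, and adjustment is useful when it does. A rule driven by observed differences can admit variables that do not matter and leave out a strong predictor that happens to look balanced. In a trial of about 100 patients, a prognostic imbalance can also be real and still go unflagged.

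Ordinary ANOVA and chi-square tests treat patients as independent, although ten units are randomised. Their p-values are therefore too small when patients within a unit resemble one another.

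Two things are at stake. The primary estimate depends on which differences appear and on who decides that correction is needed. And the precision available from a baseline score that is already collected is not secured. The first matters more than usual here because the Discussion expects selection bias in the experimental units and offers this correction as the statistical answer to it.

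**Working it through.** **1. The plan's own figures.** From the Sample size section: "an effect size of d = 0.7 is expected"; "With α = 0.05 and a power (1-β) of 0.8, 34 patients are needed per condition". A two-sided t-test calculation gives 33.02, rounded up to 34. The plan assumes 25% dropout and a rule of thumb to "increase the study population by 25% when patients are randomized at unit level". Adding the two percentages gives 34 × (1 + 0.25 + 0.25) = 51, as stated: "That means that 51 patients are required for each condition". Both figures reproduce. They are used here only to set the scale.

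**2. Effective size per arm.** Completers: 51 × 0.75 = 38.25. Reading the plan's 25% as a design effect of 1.25: 38.25 / 1.25 = 30.6.

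**3. Power with and without baseline BDI-II.** Adjusting for a baseline score with correlation r to follow-up multiplies the outcome variance by 1 − r², so the effective n becomes 30.6 / (1 − r²). The documents give no r; 0.3 to 0.6 is assumed. The noncentrality is 0.7 × √(n/2), two-sided α = 0.05. It is referred to 59 df (patient-level, 2 × 30.6 − 2) or 8 df (10 units less 2 arms).

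| r | 1 − r² | Effective n per arm | Power, 59 df | Power, 8 df |
|---|---|---|---|---|
| no adjustment | 1.00 | 30.6 | 77% | 67% |
| 0.3 | 0.91 | 33.6 | 81% | 71% |
| 0.5 | 0.75 | 40.8 | 87% | 79% |
| 0.6 | 0.64 | 47.8 | 92% | 85% |

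**4. How often the baseline tests flag something by chance.** With a design effect of 1.25, a nominal 5% test that ignores units has size 2 × (1 − Φ(1.96/√1.25)) = 2 × (1 − Φ(1.753)) = 8.0%. With 10 independent baseline variables (assumed number) and no real imbalance, the chance of at least one flag is 1 − 0.95^10 = 40% without clustering and 1 − 0.9204^10 = 56% with it. With an assumed ICC of 0.05 and 102/10 = 10.2 patients per unit, the design effect is 1 + 9.2 × 0.05 = 1.46 and the size of one test is 10.5%. These are rates of flagging a baseline variable, not false-positive rates for the SAM effect.

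**5. What test-then-adjust does to the primary test.** Simulation of 20,000 trials per setting: 5 units per arm, 8 completers per unit, unit-level inference on 8 df. The conditional rule adjusts for baseline BDI-II only if an ordinary t-test at baseline gives p < 0.05. No systematic selection was built in.

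| ICC, r | Power: never adjust | Adjust if flagged | Always adjust | Type I error, adjust if flagged |
|---|---|---|---|---|
| 0.01, 0.5 | 0.76 | 0.77 | 0.86 | 0.046 |
| 0.05, 0.3 | 0.66 | 0.66 | 0.70 | 0.049 |
| 0.05, 0.5 | 0.65 | 0.67 | 0.77 | 0.041 |
| 0.05, 0.7 | 0.66 | 0.69 | 0.90 | 0.036 |

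Across ICC 0.01 to 0.10 and r 0.3 to 0.7, the type I error of the conditional rule was 0.032 to 0.049. A further simulation with 10 baseline variables (assumed r = 0.5 for BDI-II and 0.15 for the others; 8,000 trials per setting) gave 4.3% to 4.6%. The conditional rule therefore does not inflate the error rate in these settings, and it recovers little of the available power.

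**The case against.** The strongest reply is that this is a condensed article, and that covariate lists and model form are usually left to a full protocol or analysis plan. That is fair for what the article leaves out. It does not cover what the article states, which is a rule for choosing corrections from observed differences.

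Other parts of the reply stand and limit the point:

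- **The trigger is inferred.** A reader may take the plan to say that p < 0.05 at baseline decides adjustment. It does not. That follows only from the tests and the correction sitting in adjacent sentences. Any reading still leaves the choice to the data.
- **Anxiety is named in advance,** for a prognostic reason, so not every covariate is picked afterwards.
- **Baseline BDI-II may already be in the model.** It is measured at all three times, and success is defined as a decrease relative to control. If T0 is a repeated outcome with a common baseline mean, most of the power gain is already there. If change scores are meant, it is not: their variance factor is 2(1 − r), that is 1.40, 1.00 and 0.80 at r = 0.3, 0.5 and 0.6, against 0.91, 0.75 and 0.64 with adjustment. The article does not settle which, so a reader should not conclude that baseline BDI-II is excluded.
- **Imbalance may not be chance.** The Discussion expects systematic selection, so looking at baseline differences has more purpose here than under individual randomisation with concealed allocation. That argues for fixing the relevant variables now; significance is a poor screen for systematic imbalance too.

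A reader might also infer that a data-driven model leaves the type I error uncontrolled. The simulations do not support that. They assume no selection; with selection, the problem is bias from imbalance left uncorrected, which fixing the covariates addresses only for the variables measured.

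**Conclusion.** The point holds in a limited form. The article lets observed baseline differences determine the primary adjustment, in two wordings of different scope, after tests that ignore the units. Apart from anxiety at an unstated time point, it fixes no covariate and does not commit to baseline BDI-II. The consequences are an estimate that depends on the data, prognostic imbalance that can go uncorrected, and lost precision.

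The gain forgone at d = 0.7 runs from about 4 points at r = 0.3 to 15 points (patient-level) or 18 points (8 df) at r = 0.6. It rests on an assumed correlation, on reading the plan's 25% as a design effect, and on a model that does not already use T0 efficiently. The case for naming covariates in advance does not depend on those assumptions. This should be changed, but it does not invalidate the trial.

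**What to change.** In Statistical analyses, replace the correction sentence with a fixed covariate set for the primary multi-level model, included whatever the observed balance:

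- BDI-II at T0. If T0 is instead modelled as a repeated outcome with a common baseline mean, say so.
- HADS-A at T0, which makes the anxiety covariate explicitly the baseline value.
- A short list of prognostic variables chosen now, including those likely to drive nurse-influenced selection. Former episodes, former treatment and psychiatric co-morbidity are already collected at baseline and are candidates.

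Report baseline characteristics by arm descriptively, without significance tests. Keep any further adjustment prompted by observed imbalance as a labelled sensitivity analysis, and bring the Discussion sentence into line.

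The cost is wording only. Both scores are already scheduled at T0, and no new data or patients are needed. The choice should be recorded before outcome data are examined by arm.

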### Sample size

Effect sizes (d) will be used to calculate the sample size. A meta-analysis by Cuijpers et al. [10] found an overall effect size of d = 0.87 in favor of Behavioral Activation (BA) compared to a waiting list condition. A study in an inpatient population found an effect size of d = 0.73 in favor of BA compared to supportive therapy [18].

Our study will be performed in an inpatient elderly population with severe MDD. Because of the large effect sizes in previous studies, an effect size of d = 0.7 is expected. With α = 0.05 and a power (1-β) of 0.8, 34 patients are needed per condition. In other studies [10,40], the dropout rate shows a large variability (2% – 50%). For this study, we assume an average drop-out rate of 25%. Another rule of the thumb is to increase the study population by 25% when patients are randomized at unit level. That means that 51 patients are required for each condition. In total, 102 patients will be included in this study. The sample size was calculated using the G*power 3.0 software program [41].

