**Methods/design:**

The study is designed as a multi-center cluster randomized controlled trial. BA, described as The Systematic Activation Method (SAM) will be compared with Treatment as Usual (TAU). We aim to include ten mental health care units in the Netherlands that will each participate as a control unit or an experimental unit. The patients will meet the following criteria: (1) a primary diagnosis of Major Depressive Disorder (MDD) according to the DSM-IV criteria; (2) 60 years or older; (3) able to read and write in Dutch; (4) have consented to participate via the informed consent procedure. Based on an effect size d = 0.7, we intend to include 51 participants per condition (n = 102). The SAM will be implemented within the experimental units as an adjunctive therapy to Treatment As Usual (TAU). All patients will be assessed at baseline, after eight weeks, and after six months. The primary outcome will be the level of depression measured by means of the Beck Depression Inventory (Dutch version). Other assessments will be activity level, mastery, costs, anxiety and quality of life.

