The most common treatment modalities for MDD are antidepressant medication and psychological interventions (or a combination thereof) [7]. Antidepressants seem to be efficacious in treating late-life depression, although the treatment outcomes may be less positive for the subpopulation of older elderly [8]. There are several psychotherapeutic options in depression treatment. Among adults in general, these different options are comparable in their effectiveness [9]. Recently, Behavioral Activation (BA) has gained renewed attention as an effective treatment modality in MDD. In BA, patients learn techniques to monitor their mood and daily activities and to gain insights into the connection between the two. The patients then learn how to develop a plan that increases the number of pleasant activities and positive interactions with their environment. A meta-analysis has demonstrated large effect sizes for BA interventions (d = 0.89) when compared to a waiting list condition [10]. Furthermore, direct comparisons between Cognitive Therapy (CT) and BA have demonstrated that the effectiveness of the two interventions is comparable [11,12]. Since BA seems to be more accessible for many patients than CT, BA might be a preferred treatment option. Another meta-analysis shows that, in general, psychotherapy seems to be as effective for older individuals as for younger adults [9]. However, this meta-analysis did not include studies focusing on severely depressed or hospitalized patients. In general, psychological treatments have been found to be less effective in outpatients with chronic depression [13], and possibly severe depression [14], although the evidence is not conclusive [15].

Inpatient treatment remains an important treatment option for patients who cannot safely stay in their own environment [16]. Many of these patients suffer from severe and chronic forms of depression, and effective treatment options are needed to improve their recovery and reduce their suffering. The number of studies on psychological treatment for inpatients is limited. Recently, we summarized those studies in a meta-analysis and demonstrated small but robust effects [17]. However, there was a considerable variation in treatment setting, content of treatment, number of sessions, and inclusion and exclusion criteria applied. Furthermore, the quality of most of the studies was not optimal.

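### The 51 per condition adds the drop-out and clustering allowances instead of compounding them and leaves the ten randomised units out, so 102 patients give less than the implied 80% power

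*Protocol article*

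**What the plan says.** The Sample size section of the protocol article sets out the whole derivation. It expects d = 0.7 and states: "With α = 0.05 and a power (1-β) of 0.8, 34 patients are needed per condition". It then assumes an average drop-out of 25% and adds a clustering allowance: "Another rule of the thumb is to increase the study population by 25% when patients are randomized at unit level". The conclusion follows directly: "That means that 51 patients are required for each condition", and "In total, 102 patients will be included in this study". The abstract repeats 51 per condition and 102 in total.

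Three other statements matter here. The section on units and randomisation says that ten units are randomised, matched in pairs with one unit of each pair to each condition. The Discussion confirms five SAM units. The Statistical analyses section plans multi-level analyses because randomisation is at unit level. The sample size calculation uses neither the number of units nor their size.

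**The concern.** Two things look wrong.

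- **The inflation step.** The allowances appear to have been summed. To have n patients left after losing a quarter, one must enrol n / 0.75, not n × 1.25. A clustering factor then multiplies that result.
- **The number of units.** A flat percentage added to an individually randomised calculation makes no allowance for estimating between-unit variation from only ten units. The critical value for the arm effect can then be clearly larger than the one behind the 34.

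SAM is to be called effective on the strength of a significant difference from TAU. A reader who takes the trial to have 80% power at d = 0.7 would give a non-significant result more weight than the design supports.

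**Working it through.** **Inputs from the protocol article:** d = 0.7, α = 0.05, power 0.8, 34 per condition, 25% drop-out, 25% clustering increase, 51 per condition (Sample size); ten units in matched pairs (units and randomisation); five SAM units (Discussion).

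**Assumptions of this check:** two-sided test (two-sided reproduces 34, one-sided would give 26); equal unit sizes; degrees of freedom for the arm effect, where taken at unit level, of 10 − 2 = 8.

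**1. Base size.** Two-sample t-test, noncentral t: n = 33 gives 79.97% and n = 34 gives 81.2%. The 34 is reproduced.

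**2. Inflation.** Four ways to apply the two allowances:

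| Rule | Result | Rounded up |
|---|---|---|
| 34 × (1 + 0.25 + 0.25) | 51.0 | 51 |
| 34 × 1.25 × 1.25 | 53.1 | 54 |
| 34 / 0.75 + 0.25 × 34 | 53.8 | 54 |
| 34 × 1.25 / 0.75 | 56.7 | 57 |

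Only simple addition gives 51. The last line is what the two allowances require.

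**3. Effective size left by 51.** Completers per arm: 51 × 0.75 = 38.25. Divided by a design effect of 1.25: 38.25 / 1.25 = 30.6, against the 34 needed.

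**4. The more favourable reading of the 25%.** Suppose the 1.25 belongs to the enrolled unit size, 51 / 5 = 10.2. The implied ICC is 0.25 / 9.2 = 0.027. With 38.25 / 5 = 7.65 completers per unit, the design effect is 1 + 6.65 × 0.027 = 1.18, which leaves 38.25 / 1.18 = 32.4 effective patients per arm.

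**5. Power at d = 0.7.** The noncentrality is 0.7 × √(n_eff / 2); for 30.6 it is 0.7 × √15.3 = 2.74.

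| Effective n per arm | Patient-level df | 8 df |
|---|---|---|
| 30.6 (design effect 1.25) | 76.8% | 67.1% |
| 32.4 (design effect 1.18) | 79.2% | about 70% |
| 38.25 (ICC = 0) | not needed here | 76.5% |

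The two-sided critical value is about 2.00 with patient-level df and 2.31 with 8 df. That difference alone accounts for most of the drop. It is why 8 df falls short of 80% even with no clustering at all.

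**6. Detectable effect at 80% power, n_eff = 30.6:** d = 0.73 with patient-level df, 0.82 with 8 df.

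**7. What 57 per arm would give.** 57 × 0.75 / 1.25 = 34.2 effective per arm: 81.4% with patient-level df, but only 71.8% with 8 df.

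**The case against.** The inflation error alone is small. It costs six patients per arm and about 1 to 3 points of power. On a normal approximation, 30.6 effective patients give 78.2% and 32.4 give 80.5%. This stands, and it means that the compounding error on its own would be minor.

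The larger shortfall rests on 8 df, which the article does not state. It says only that analyses will be multi-level, and the method for degrees of freedom is commonly left to an analysis plan. This also stands, so the 67% to 70% must be labelled as conditional. It does not remove the point that the printed calculation leaves out the number of units.

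Adjustment for baseline BDI-II could recover power. At an assumed baseline-outcome correlation r of 0.3 to 0.5, applied to the whole variance, n_eff = 30.6 is divided by 1 − r². Power becomes about 81% to 87% (patient-level) or 71% to 79% (8 df). However, the sample size section claims no such gain, and the analysis section commits to correcting baseline differences only where necessary.

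A reader might be tempted further in two directions, and the documents support neither.

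- **Fewer degrees of freedom still, because units are matched in pairs.** The article uses pairs for allocation but does not say that they enter the model. A lower figure would also have to assume that matching brings no reduction in variance, which is the purpose of matching.
- **That d = 0.7 is contradicted by the Background**, where the authors write that "we summarized those studies in a meta-analysis and demonstrated small but robust effects". That meta-analysis covers psychological treatments of inpatients in general, with considerable variation and limited study quality. The d = 0.73 study was itself in inpatients and tested behavioural activation against supportive therapy. With 25 patients it is weak support, but the choice of d is a planning judgement, and the article gives no smaller numerical effect to set against it.

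**Conclusion.** The point holds in limited form. The 51 per condition does not follow from the article's own inputs: the two allowances were added where compounding gives 57. On those allowances, 102 patients give about 77% power at d = 0.7 with patient-level degrees of freedom, or about 79% on the more favourable reading of the clustering factor.

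The weightier omission is that ten randomised units play no part in the calculation. With about 8 df, power is about 67% to 70%, and about 76% even at an ICC of 0. These figures assume a two-sided test, equal unit sizes, df equal to units minus two, and no gain from baseline adjustment.

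A reader might infer that the trial cannot reach 80% power under any analysis. The documents do not support that, because baseline adjustment could close part or all of the gap, depending on a correlation that the article does not give. A reader might also infer that 57 per arm is the correct size. It repairs only the compounding.

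**What to change.** Keep n = 102 and change the text of the Sample size section, with the abstract in line. Either:

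- state that 51 per condition gives about 77% power at d = 0.7 after 25% drop-out and a 25% clustering allowance, and about 67% if the arm effect is tested with about 8 df for ten units; or
- state the effect detectable at 80% power as d of about 0.73, or about 0.82 at 8 df.

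In both cases, label the 8 df as an assumption and say that the figures precede any baseline adjustment. If a required size is still given, replace 51 by 57 and add that 57 per arm corrects only the compounding and gives about 72% at 8 df.

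The cost is a less favourable stated power. No extra patients or units are needed, and the conduct of the trial does not change.
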